## Abstract

**Introduction:**

Chronic musculoskeletal pain bothers the quality of life for approximately 1.71 billion people worldwide. Although pharmacological therapies play an important role in controlling chronic pain, overuse of opioids, persistent or recurrent symptoms, and pain-related disability burden still need to be addressed. Heat-stone massage is using the heated stone to stimulate muscles and ligaments followed by massage for relax, which can potentially treat the chronic musculoskeletal pain. To determine the efficacy and safety of heat-stone massage for patients with chronic musculoskeletal pain is needed.

**Methods and analysis:**

This multicenter, 2-arm, randomized, positive drug-controlled trial will include a total of 120 patients with chronic musculoskeletal pain. The intervention group will receive a 2 week heat-stone massage, 3 times per week, whereas the control group will receive the flurbiprofen plaster twice per day for 2 weeks. The primary end point is the change in Global Pain Scale from baseline to the end of the 2 week intervention. The secondary outcomes include the pain severity (Numerical Rating Scale), pain acceptance (Chronic Pain Acceptance Questionnaire), self-management (Health Education Impact Questionnaire), self-efficacy (Pain Self-Efficacy Questionnaire), anxiety and depression (Hospital Anxiety and Depression Scale), quality of life (Short Form-36). The intention-to-treat dataset will be used for analysis.

**Discussion:**

The pain management remains the research topic that patients always pay close attention to. This will be the first randomized clinical trial to evaluate whether heat-stone massage, a non-pharmacological therapy, is effective in the chronic musculoskeletal pain management. The results will provide evidence for new option of daily practice.

**Clinical trial registration:**

World Health Organization Chinese Clinical Trial Registry [ChiCTR2200065654; https://www.chictr.org.cn/showproj.html?proj=185403]; International Traditional Medicine Clinical Trial Registry [ITMCTR2022000104; http://itmctr.ccebtcm.org.cn/en-US/Home/ProjectView?pid=51776b6f-77b8-4811-9b5a-a0fec10f2cee].

## Introduction

Chronic musculoskeletal pain, affecting bones, muscles, ligaments, tendons, and joints, bothers the quality of life for approximately 1.71 billion people worldwide, according to the report of World Health Organization (1). Virtually everyone, over the course of life span, has some form of musculoskeletal pain (2). Because of its negative impact on the locomotor system, chronic musculoskeletal pain particularly the low back pain is the leading contributor to disability in 160 countries (3, 4). Moreover, the chronic pain can significantly increase the overuse of drug consumption, higher frequency of sick leave, earlier retirement from work, and can reduce the well-being levels and society participation capacity (5).

Pharmacological therapies include simple analgesics, opioids, and adjuvant, which were originally proposed by WHO known as the pain ladder system, based on the management guideline of musculoskeletal pain (2). Although these therapies play an important role in chronic pain management, their efficacy can be sometimes limited, and there is safety concern. A systematic review summarized the common problems in musculoskeletal pain care--overuse of imaging, overuse of surgery, overuse of opioids, and failure to provide education and advice (6). Despite multiple first-line therapies recommended in chronic musculoskeletal pain guidelines, many patients still suffer from persistent or recurrent symptoms, leading to the trend that the burden disability caused by chronic pain in patients with chronic musculoskeletal disorders had increased by 46% since 1990 until 2010 in 21 regions worldwide (7). Although the guideline suggests non-pharmacological therapies such as physical modalities, cryotherapy, heat therapy, transcutaneous, and acupuncture, researchers and primary care providers still highly recommends that apply manual therapy only as an adjunct to other evidence-based treatment, indicating there is lack of evidence for these non-pharmacological therapies.

Heat-stone massage is using the heated stone to stimulate the muscles, ligaments, and tendons, followed by massage for relaxation. In the framework of Chinese medicine theory, chronic musculoskeletal pain can be regarded as local stagnancy and lack of nourishment in the related meridians; meanwhile, heat can be used to nourish the meridians, stone can be used to stimulate the acupoints to smooth the stagnancy, and massage can relax the local tissue after the heat-stone stimulations to enhance the pain relief. One clinical trial with 56 participants enrolled showed that focal massage with high force significantly lower visual analog scale compared with low force (mean difference of −1.33) (8). Another clinical trial with a total of 78 participants showed that moxibustion-*cum*-massage significantly reduced the pain severity assessed by brief pain inventory compared to control group of no treatment (mean difference of −0.76) (9). Our *unpublished* pilot study showed that heat-stone massage reduced the pain assessed by global pain scale (GPS) by a mean of 4. We hypothesis that this novel heat-stone massage would reduce pain level in patients with chronic musculoskeletal pain. This randomized controlled trial is aimed to investigate the efficacy and safety of heat-stone massage for patients with chronic musculoskeletal pain.

## Methods and analysis

### Study design

This study is a randomized, positive drug controlled, clinical trial, which will include a total of 120 patients with chronic musculoskeletal pain. Potential participants who are diagnosed by chronic musculoskeletal pain based on categories in International Classification of Diseases version 11 (ICD-11) for both inpatient and outpatient settings will be screened for eligibility criteria. All included patients will be randomly assigned into either the heat-stone massage group or positive drug control (flurbiprofen plaster) group at a 1:1 ratio. The primary outcome is the pain level assessed by global pain scale. This protocol is in accordance with the Standard Protocol Items: Recommendations for Interventional Trials reporting guideline (SPIRIT) (10).

### Participants recruitment

This clinical trial is being conducted in Guang’anmen Hospital, China Academy of Chinese Medical Sciences (Beijing, China), the First Affiliated Hospital of Henan University of Chinese Medicine (Henan, China), and Chongqing Traditional Chinese Medicine Hospital (Chongqing, China). The study has been recruiting patients since November 2022. We expect the study can be complete in September 2024. Participants are screened at outpatient pain clinic or in the hospital ward. Research staff will visit potential participants who meet the criteria and give them a comprehensive introduction to our study aim and protocol and invite them to join the study. All participants will sign the informed consent form before formal enrollment in our study. The study workflow chart is shown in Figure 1.

**Figure 1 fig1:**
[figure not shown]
Flow diagram of the study protocol. NRS, Numerical rating scale; GPS, Global pain scale; CPAQ, Chronic pain acceptance questionnaire; heiQ, Health Education Impact Questionnaire; PSEQ, Pain Self-Efficacy Questionnaire; HADS, Hospital anxiety and depression scale; SF-36, Short Form-36.

### Inclusion and exclusion criteria

The inclusion criteria of this trial are (1) chronic primary musculoskeletal pain is clinically diagnosed based on the criteria that chronic primary musculoskeletal pain is chronic pain in the muscles, bones, joints or tendons that is characterized by significant emotional distress such as anxiety, anger/frustration or depressed mood or functional disability such as interference in daily life activities and reduced participation in social roles, including fibromyalgia syndrome which is defined as diffuse pain in at least 4 of 5 body regions which is associated with significant emotional distress or functional disability; (2) chronic musculoskeletal pain symptoms more than 3 months; (3) pain severity of Numerical Rating Scale (NRS) pain score between 4 and 6; (4) pain is often related to weather changes, and symptoms can be aggravated after rainy days and fatigue; (5) age between 18 years and 80 years; (6) volunteer to participate in the trial and sign the informed consent.

The exclusion criteria of this trial are (1) acute pain or chronic secondary musculoskeletal pain or chronic cancer related pain or chronic neuropathic pain; (2) history of cardiovascular and cerebrovascular diseases, liver diseases, kidney diseases, blood system diseases, diabetes, or infectious diseases; (3) history of tuberculosis, rheumatoid arthritis, ankylosing spondylitis, gout, or cancer bone metastasis; (4) history of mental disorders or communication dysfunction; (5) history of peripheral nerve perception disorder; (6) pregnant, lactating women or those who have pregnancy plans; (7) surgical plan in the next 3 months; (8) reported allergy to the interventions in this trial; (9) have used pain killers or received other pain treatment within the last 1 week.

### Randomization and blinding

All the included participants will be randomly assigned to the heat-stone therapy group (treatment group) or the flurbiprofen plaster group (control group) with a 1:1 ratio with a block size of 6 (R, version 4.2.0). The statistician in our team ([name]) will produce the randomization number list for 3 trial centers, respectively, using central randomization system at the Clinical Assessment Center of China Academy of Chinese Medical Sciences, then randomization list will be automatically sealed in the system including the treatment assignment in it, which will not be seen by any other research staff. This statistician who oversees the randomization will not participate in any process of data collection or outcome analysis. A study nurse in our team ([name]) who is not involved in the randomization number generation or patient recruitment process, will use the randomization sequence in the central randomization system to assign the patients in the outpatient or inpatient centers of the hospital in person. Then the patients will be randomly assigned into the heat-stone massage group or flurbiprofen plaster group. Both the participants and heat-stone massage therapists are aware of the treatment, but the principal investigator of this trial, outcome assessment research staff and data analysis statistician will be blinded to the randomization.

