### Power analysis and sample size calculation

The power analysis and sample size estimation were based on the primary outcome of this trial which is the change in GPS from baseline to the end of the 2 week intervention. One of our pilot studies showed that the mean change in GPS in heat-stone group was 12, while the mean change in GPS in flurbiprofen was 8, with a combined standard deviation of 6.7. With a power of 80%, 2-sided alpha of 0.05, and the assumption that the change is normally distributed, we used the “power twomeans” function in STATA with 1:1 ratio in treatment and control group to get estimated sample size of 46 samples for each group, so that a total of 92 participants are required. Considering the 20% dropout rate, the total sample size of 115 is required. To make it convenient to assign the participants with 2:1:1 ratio to the 3 centers, we took the 120 as the final planned sample size. The sample size was calculated using STATA, version 16.1 (StataCorp, USA).

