### Statistical analysis

The Primary analysis will be conducted on the full dataset of all the participants after randomization based on the intention-to-treat principle. Moreover, sensitivity analysis will be conducted between the full dataset and the per protocol dataset. Participants who are not in the per protocol analysis are nonadherence which might be caused by failure to receive the assigned treatment, suffering from severe adverse events, or loss of follow-up.

To check if there is selection bias and confounding factors, we will compare the baseline characteristics of the two groups. Continuous variables will be described as mean (Standard Deviation) for normal distribution and be tested using t test or be described as median (interquartile range) for skewed distribution and be tested using Mann–Whitney test. Categorical variables will be summarized as counts (percentages) and be tested using Chi squared test or Fisher exact test.

The primary outcome of this trial is the change in Global Pain Scale from baseline to the end of the 2 week intervention. The difference of the changes between the two groups will be analyzed using a generalized linear mixed model. The mean and 95% confidence interval will be calculated and estimated. Known confounding factors that may affect the pain severity in chronic musculoskeletal patients include age, sex, job, duration of the chronic pain, and emotional state. Therefore, we will make the subgroup analysis for the variables of age categories (>60 years vs. ≤60 years), sex (female vs. male), job categories, duration of pain, taking these as covariates in the model.

For the secondary outcomes, generalized linear mixed model will be used for continuous variables, and two proportion z test will be used for proportions, whereas the Chi squared test or Fisher exact test will be used for categorical variables.

The primary economic analysis will be the cost-utility analysis over 6 week using quality-adjusted life years (QALYs) calculated from the SF-36. The mixed-effect linear regression model will be used, adjusting the confounding factors including age, sex, job, and site of recruitment.

All statistical tests will use the statistical significance of 2-sided *p* value of <0.05. All the statistical analysis will be performed using Python, version 3.8.16 (sklearn and statsmodels packages).

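### Randomisation is stratified by centre, but the primary GPS model does not name centre; if centre is left out and matters, the test is mildly conservative

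*Protocol article*

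**What the plan says.** Randomization and blinding: the statistician will "produce the randomization number list for 3 trial centers, respectively, using central randomization system", and patients are allocated "with a 1:1 ratio with a block size of 6". One list per centre with permuted blocks is randomisation stratified by centre.

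Power analysis and sample size calculation: the total is rounded up for the planned split over centres, "To make it convenient to assign the participants with 2:1:1 ratio to the 3 centers, we took the 120 as the final planned sample size". That is 60, 30 and 30 patients, each a whole number of blocks of 6.

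Statistical analysis, primary outcome: "The difference of the changes between the two groups will be analyzed using a generalized linear mixed model". The random effects of that model are not stated. The variables then listed are age category, sex, "job categories, duration of pain, taking these as covariates in the model". Centre is not among them.

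Statistical analysis, economic evaluation: a mixed-effect linear regression is used, "adjusting the confounding factors including age, sex, job, and site of recruitment". This is the only model for which site is named.

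**The concern.** An analysis should normally reflect the factors that restricted the randomisation. When arms are balanced within each centre, differences between centres largely cancel out of the treatment comparison, so the true sampling variance of the treatment difference falls. A model without centre still counts those differences as residual noise. Its standard error is then larger than the real variability of the estimate, its confidence interval is too wide and its p-value too large.

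The article makes one wonder whether this was intended, because site appears as an adjustment factor in the economic model a few lines after it is absent from the primary one. The trial is sized for 80% power, so an avoidable loss of precision is worth removing. A centre effect is plausible: the three hospitals are in Beijing, Henan and Chongqing, and the intervention is delivered by hand by each site's own providers. That is inference; the article reports no difference between centres.

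**Working it through.** **Inputs from the article.** Expected changes: "the mean change in GPS in heat-stone group was 12, while the mean change in GPS in flurbiprofen was 8", a difference of 12 − 8 = 4. SD 6.7, two-sided alpha 0.05, power 80%, dropout 20%, blocks of 6, centres of 60/30/30.

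**Assumed input.** R², the share of variance in GPS change that lies between centres. The article does not give it; the range examined is 0 to 0.20.

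**Step 1: the plan's own figure.** The exact t-test calculation with difference 4 and SD 6.7 gives power 79.98% at 45 per arm and 80.9% at 46. So 46 per arm and 92 in total reproduce, and 92 / 0.80 = 115. The sample size is sound.

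**Step 2: standard error with full balance.** The true sampling SD of the treatment difference is the centre-free model's standard error times √(1 − R²). The standard error is therefore too large by a factor 1/√(1 − R²):
- R² = 0.05: 1/√0.95 = 1.026, or 2.6% too large.
- R² = 0.10: 1/√0.90 = 1.054, or 5.4% too large.

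**Step 3: type I error with full balance.** 2 × [1 − Φ(1.96/√(1 − R²))]:
- R² = 0.05: 0.044.
- R² = 0.10: 0.039.

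**Step 4: power at 46 per arm, both analyses under the same centre effect.** The standard error without centre is 6.7 × √(2/46) = 1.397, so the standardised difference is 4/1.397 = 2.863. The critical t value on 90 degrees of freedom is 1.987.
- Centre in the model: the noncentrality is 2.863/√(1 − R²), and power is 82.8% (R² = 0.05) and 84.7% (R² = 0.10).
- Centre omitted: the estimate has the same smaller sampling variance, but the threshold stays at 1.987 of the larger standard error. Power is approximately 81.5% and 82.1%.
- Gain from including centre: about 1.3 and 2.7 points.

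**Step 5: simulation with the actual design.** 15,000 runs per setting, permuted blocks of 6 within centres of 60/30/30, fixed centre effects. Each pair is centre omitted / centre included.

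| R² | Type I error, no dropout | Type I error, 20% dropout | Power, 20% dropout |
|---|---|---|---|
| 0 | 0.048 / 0.049 | 0.050 / 0.050 | 82.6% / 82.4% |
| 0.02 | 0.049 / 0.051 | 0.051 / 0.053 | 82.7% / 83.2% |
| 0.05 | 0.045 / 0.050 | 0.047 / 0.052 | 83.0% / 84.2% |
| 0.10 | 0.039 / 0.048 | 0.041 / 0.050 | 84.1% / 86.7% |
| 0.20 | 0.029 / 0.052 | 0.036 / 0.054 | 83.7% / 89.4% |

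Simulation error on a type I figure is about √(0.05 × 0.95/15,000) = 0.002. Dropout disturbs the balance within centres, so conservatism is milder than the formulas of steps 2 and 3 suggest. The power gain with dropout is 1.2 points at 5% and 2.6 points at 10%, in line with step 4.

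**The case against.** The strongest objection is that the article does not say centre is absent. The primary analysis is a mixed model whose random effects are not described, and centre is a natural candidate, as is the patient for repeated visits. A condensed article may leave that to the full plan. This stands: if the full plan has a centre term, only the wording needs to change. It does not remove the point, because the article names site for one model and not for the one that matters most.

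The sentence that ends "taking these as covariates in the model" is also worded around subgroup analysis, so it cannot be read as a closed covariate list for the primary model.

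A reader might go further and conclude that the primary standard errors are too large and the confidence intervals wrong. The documents do not support that. The excess arises only if GPS change differs between centres, and no figure for this is given. Entry restricted to pain scores of 4 to 6, an outcome measured as change, and common staff training could all keep such differences small. Nothing in the article says that case mix differs by centre.

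It is also tempting to compare the planned 80.9% power with 82.8% and 84.7% and claim gains of 1.9 and 3.8 points. That is not like for like: 80.9% is the power when centre explains nothing, and the centre-free test also gains some power when centre matters.

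Finally, a centre main effect does not address a massage effect that itself varies by centre. That is an interaction and a separate question.

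**Conclusion.** The point holds in conditional form. The design stratifies by centre, and the article does not name centre for the primary model. The sizes given depend on the assumed 5% to 10% share of variance between centres. Over that range the consequence is modest, and the error is on the cautious side. At 20%, the upper end of the range examined, the simulated power loss with dropout is about 6 points (83.7% against 89.4%). With no centre effect, including centre costs practically nothing (82.6% against 82.4%, within simulation error). This is an inexpensive improvement and a clarification, not evidence that the primary result would be invalid.

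**What to change.** State in the analysis section that centre enters the primary GPS model, and the models for the continuous secondary outcomes, as a 3-level fixed effect. A fixed effect is preferable to a random one because three centres are too few to estimate a between-centre variance usefully. If the full plan already includes centre, say so and in what form.

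For consistency, the responder outcome on the Numerical Rating Scale can be analysed with a centre-stratified (Mantel-Haenszel) risk difference in place of the plain two-proportion z test. No calculation was made for that outcome.

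The cost is a change of wording and two degrees of freedom (90 to 88 at 46 per arm). No change to sample size or data collection is needed. Make the change before unblinding, so that adding centre cannot look data-driven.

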### Baseline assessment

Baseline visit and assessment will be conducted at the inpatient centers in the hospitals. Demographic information (including sex, age, educational background, job), course of the chronic pain, medical history (including complications, smoking, alcohol), and basic tests (including blood pressure, heart rate), will be collected in person. Baseline assessment about the chronic musculoskeletal pain will include severity of the pain (assessed by Numerical Rating Scale, range 0–10, higher scores indicate worse pain), pain-related overall life assessment (measured by Global Pain Scale, range 0–200, higher scores indicate worse influence on life), acceptance of pain (assessed by Chronic Pain Acceptance Questionnaire, range 0–120, higher scores indicate higher pain acceptance), health education and self-management (assessed by the Health Education Impact Questionnaire, range 40–200, higher scores indicate better health self-management), pain-related self-efficacy (assessed by the Pain Self-Efficacy Questionnaire, range 0–60, higher scores indicate better confidence of self-efficacy), anxiety and depression (assessed by the Hospital Anxiety and Depression Scale, range 0–42, higher scores indicate more severe symptoms), and quality of life (assessed by Short Form-36, range 0–100, higher scores indicate better health). All scheduled visits are shown in the Table 1.

**Table 1 tab1:** The schedule of planned visits.

Study component	Visit 1	Visit 2	Visit 3	Visit 4	Visit 5	Visit 6	Visit 7	Visit 8
Time	1 d before treatment	First treatment	7 ± 1 d after treatment	14 ± 1 d after treatment	21 ± 1 d after treatment	28 ± 1 d after treatment	35 ± 1 d after treatment	42 ± 1 d after treatment
Informed consent	×	–	–	–	–	–	–	–
Demographic	×	–	–	–	–	–	–	–
Pain duration	×	–	–	–	–	–	–	–
Pain locations	×	–	–	–	–	–	–	–
Pain triggers	×	–	–	–	–	–	–	–
Randomization	×	–	–	–	–	–	–	–
Intervention	–	×	×	×	–	–	–	–
NRS	×	–	×	×	–	–	–	×
GPS	×	–	×	×	–	–	–	×
CPAQ	×	–	×	×	–	–	–	×
heiQ	×	–	×	×	–	–	–	×
PSEQ	×	–	×	×	–	–	–	×
HADS	×	–	×	×	–	–	–	×
SF-36	×	–	×	×	–	–	–	×
Pain killer intake	×	–	×	×	–	–	–	×
Adverse events	–	×	×	×	×	×	×	×

NRS, Numerical rating scale; GPS, Global pain scale; CPAQ, Chronic pain acceptance questionnaire; heiQ, Health Education Impact Questionnaire; PSEQ, Pain Self-Efficacy Questionnaire; HADS, Hospital anxiety and depression scale; SF-36, Short Form-36.

